## Study Design and Trial Outcomes

A cluster feasibility randomized trial will be conducted in Hung Yen province, Vietnam to evaluate the feasibility and acceptability of a novel community-based intervention using the “storytelling” method to enhance the control of HTN in adults residing in 4 rural communities.

Feasibility outcomes include recruitment, retention, engagement, and treatment fidelity. Exploratory outcomes will include levels of systolic and diastolic BP and the proportion of participants with controlled BP defined as in JNC-8 at three months after randomization.

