### *Study Outcomes*

Feasibility outcomes include recruitment, retention, engagement, and treatment fidelity. Recruitment rates will be calculated from the number of patients approached and reasons for ineligibility and non-participation. We will record the number and reasons for failure to complete the follow-up assessment. Intervention engagement, which will be mainly ascertained from the patient survey as described above, includes time spent watching the

DVD, satisfaction with the viewing experience, and “transportation” into the story line.

Treatment fidelity will be determined by the Vietnam Co-PIs directly monitoring 20% of all study enrollment and follow-up visits and completing a fidelity checklist which will be carefully documented. Exploratory outcomes will include levels of systolic and diastolic BP and the proportion of participants with controlled BP defined as in JNC-8 ( $\leq 140/90$  mmHg for all individuals –a different cut-off will be used for those patients  $\geq 60$  years old and do NOT have diabetes and do NOT have chronic kidney disease for whom BP should be  $\leq 150/90$  mmHg) at three months after randomization.

The recruitment and retention rates of study participants will be calculated for each follow up visit in order to implement the intervention in a timely manner. Given our previous survey data about an individual’s willingness to participate in a clinical trial of HTN conducted at this study site, these rates are anticipated to be greater or equal to 80%. Examination of our final recruitment and retention rates will allow us to focus on specific aspects of the study protocol that need to be revised. Patient’s engagement and treatment fidelity will be collected through a questionnaire survey. Based on patient’s feedback, we will revise the intervention accordingly. We anticipate that changes in BP from baseline enrollment would be 2 mmHg or greater among those in the intervention than in the control group. Based on these findings, we will carry out sample size estimates to have adequate power to detect meaningful between group differences in our pre-specified major trial endpoints.

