## **Data Analysis Plan**

Baseline characteristics of the intervention and usual care groups will be summarized using standard descriptive statistics. We will examine extent and mechanisms of missingness in data on each measure including participant satisfaction, recruitment, retention rates, baseline assessment, and BP. We will report numbers and reasons for recruitment and retention using a CONSORT diagram[32, 33] and will report results consistent with the CONSORT-EHEALTH checklist.[34] We will conduct a directed content analysis[35] of the open-ended questions to elaborate on the quantitative measures of engagement and to identify themes of satisfaction and suggestions for improvement.

Given the feasibility nature of this study, we will have limited ability to test hypotheses of intervention effectiveness. However, we will compare the distributions of systolic and diastolic BP and rates of BP control between the intervention and comparison groups. We will examine outcome variability within and between patients over time to inform the sample size calculations for the future trial. We will calculate the intraclass correlation coefficient (ICC) that accounts for the nesting of patients within commune.[36-39]

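### The 2 mmHg expectation is on change from baseline, the BP outcome is a three-month level, and the stated comparison names no use of baseline BP

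*Protocol*

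**What the plan says.** BP appears on two metrics.

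- **Outcome definition.** The Summary (Study Design and Trial Outcomes) says "Exploratory outcomes will include levels of systolic and diastolic BP and the proportion of participants with controlled BP", and Study Outcomes repeats this with the control definition added. Both place the outcome at three months after randomization.
- **Expected effect.** Later in Study Outcomes: "We anticipate that changes in BP from baseline enrollment would be 2 mmHg or greater among those in the intervention" than in the control group. This is a difference in change. It does not say which pressure is meant.
- **Comparison.** The Data Analysis Plan says "we will compare the distributions of systolic and diastolic BP and rates of BP control between the intervention and comparison groups". It names no time point, model or covariate. The only stated between-arm use of baseline data is a descriptive summary of baseline characteristics.
- **Use of the results.** Study Outcomes continues: "Based on these findings, we will carry out sample size estimates to have adequate power to detect meaningful between group differences". The Data Analysis Plan adds: "We will examine outcome variability within and between patients over time to inform the sample size calculations for the future trial", and says that the ICC will be calculated.
- **Status.** The BP outcomes are labelled exploratory, and the Data Analysis Plan concedes: "Given the feasibility nature of this study, we will have limited ability to test hypotheses of intervention effectiveness".

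Baseline BP is collected at enrollment and again at three months under one measurement procedure (Data collection and management).

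**The concern.** The scale of the expectation does not match the scale of the outcome, and the comparison does not say which scale it follows. This matters for two reasons.

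First, only four communes are randomized, two per arm, with 25 participants each. Allocation of so few units cannot be relied on to balance baseline BP. A comparison of three-month levels that ignores baseline carries any chance imbalance forward, in proportion to how strongly follow-up BP tracks baseline BP.

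Second, the results feed the sample size of the next trial. The variance, and possibly the ICC, depend on whether the outcome is a level, a change or a baseline-adjusted value. Setting a 2 mmHg target on change against variability estimated on levels could make the future trial too large or too small.

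**Working it through.** The protocol gives no SD, ICC, alpha or power for BP, and its Sample Size section declines a power analysis. There is therefore no stated figure to reproduce, and what follows is illustration.

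**Inputs from the protocol:** k = 2 communes per arm, m = 25 participants per commune, anticipated difference 2 mmHg.

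**Assumed, not in the documents:** SD 12–20 mmHg, ICC 0–0.10, baseline-to-three-month correlation r mainly 0.5–0.7, with the same r at participant and commune level unless stated.

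**Formulas**

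- SE of an arm difference in BP level (baseline or three months) = SD × √[2(1 + (m − 1) × ICC)/(k × m)] = SD × √[0.04 × (1 + 24 × ICC)]
- Change score: SE × √[2(1 − r)]
- Baseline-adjusted: SE × √(1 − r²)
- Chance of a baseline difference above 2 mmHg in either direction = 2 × [1 − Φ(2/SE)]
- 95% half-width at cluster level: 4.30 × SE (t with 2 df)

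Example: SD 18 and ICC 0.05 give 18 × √(0.04 × 2.2) = 5.34 mmHg.

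| SD | ICC | SE, levels | P(baseline gap > 2) | Adjusted SE, r = 0.5 / 0.7 | Half-width, levels | Half-width, adjusted, r = 0.5 / 0.7 |
|---|---|---|---|---|---|---|
| 12 | 0 | 2.40 | 40% | 2.08 / 1.71 | 10.3 | 8.9 / 7.4 |
| 15 | 0.02 | 3.65 | 58% | 3.16 / 2.61 | 15.7 | 13.6 / 11.2 |
| 18 | 0.05 | 5.34 | 71% | 4.62 / 3.81 | 23.0 | 19.9 / 16.4 |
| 20 | 0.10 | 7.38 | 79% | 6.39 / 5.27 | 31.7 | 27.5 / 22.7 |

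**Gain from adjustment.** √(1 − 0.25) = 0.87 and √(1 − 0.49) = 0.71, so the SE falls by about 13% at r = 0.5 and 29% at r = 0.7. A simple change score gains nothing over levels at r = 0.5, because √[2 × 0.5] = 1. It is worse at r = 0.3: at SD 15 and ICC 0.02 its SE is 4.32 against 3.65.

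**Consequence for sizing the next trial.** Relative to levels, the variance of the arm difference is 1 − r² when baseline-adjusted (0.75 at r = 0.5, 0.51 at r = 0.7) and 2(1 − r) for change (1.4 at r = 0.3, 0.6 at r = 0.7). For a fixed target difference, required sample size scales with these factors.

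The ICC can shift as well. Take a level ICC of 0.02, a participant correlation of 0.5 and a commune correlation of 0.8. The between-commune part of the change variance is then 2 × 0.2 × 0.02 = 0.008 and the within-commune part is 2 × 0.5 × 0.98 = 0.98. The ICC for change is 0.008/0.988 = 0.008, not 0.02.

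**The case against.** The strongest reply is that the Data Analysis Plan fixes no model. A reader might infer that the protocol commits to an unadjusted comparison of three-month levels, but it does not say so. Covariates are commonly left to a SAP, and none was available here. The expectation stated as change, together with the plan to study variability over time, could even suggest that change is intended. This stands against any claim that adjustment has been ruled out. It does not remove the mismatch, which lies between two statements within Study Outcomes itself.

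A reader might also infer that level and change are rival estimands, so that the protocol contradicts itself. It does not: under randomization both have the same expected between-arm difference. They differ in precision, in sensitivity to chance imbalance and in the variance used for planning.

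Third, the comparison is exploratory, its limits are conceded, and no decision to proceed is tied to the BP difference. That lowers the stakes. It does not dispose of the sizing issue, because Study Outcomes bases the future trial's sample size on these findings.

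Finally, the SD and ICC are assumed. Entry requires elevated BP at two time points (Participant Eligibility), which may narrow the baseline spread and with it the likely imbalance.

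**Conclusion.** The point holds as a mismatch of metric with modest consequences. The expected effect is on change, the outcome is on levels, the pressure is not named, and no use of individual baseline BP is stated for the comparison. For an assumed SD of 12–20 mmHg and ICC of 0–0.10, a chance baseline gap larger than the anticipated effect has a probability of about 40–79%. That is plausible to likely, not certain, so the documents do not support saying that baseline differences will swamp the effect.

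Nor would adjustment rescue the comparison. With r at 0.5–0.7 the adjusted SE is still 1.7–6.4 mmHg and the 2-df half-width at least 7.4 mmHg. A 2 mmHg difference is out of reach mainly because there are 100 participants and two communes per arm. The value of the change lies in less sensitivity to baseline imbalance, an SE lower by about 13–29%, and planning figures on the scale the next trial will use.

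**What to change.** In Study Outcomes and the Data Analysis Plan:

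1. Define the exploratory BP comparison as the between-arm difference in three-month SBP and DBP, adjusted for the participant's own baseline value.
2. Adjust at participant level, then summarise by commune, so that 2 df remain. Using the commune's mean baseline as a covariate across four points would leave 1 df (t = 12.7) and could widen the interval sharply.
3. State the 2 mmHg on this scale and say whether it refers to SBP or DBP.
4. Report the SD, ICC and baseline-to-follow-up correlation for this metric as inputs to the future sample size.
5. Present the arm difference as descriptive, with a cluster-level interval, and say that the trial cannot detect 2 mmHg.

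The cost is wording only. Baseline BP is already collected, so no further data or visits are needed.

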## **Data Analysis Plan**

Baseline characteristics of the intervention and usual care groups will be summarized using standard descriptive statistics. We will examine extent and mechanisms of missingness in data on each measure including participant satisfaction, recruitment, retention rates, baseline assessment, and BP. We will report numbers and reasons for recruitment and retention using a CONSORT diagram[32, 33] and will report results consistent with the CONSORT-EHEALTH checklist.[34] We will conduct a directed content analysis[35] of the open-ended questions to elaborate on the quantitative measures of engagement and to identify themes of satisfaction and suggestions for improvement.

Given the feasibility nature of this study, we will have limited ability to test hypotheses of intervention effectiveness. However, we will compare the distributions of systolic and diastolic BP and rates of BP control between the intervention and comparison groups. We will examine outcome variability within and between patients over time to inform the sample size calculations for the future trial. We will calculate the intraclass correlation coefficient (ICC) that accounts for the nesting of patients within commune.[36-39]

### ***Sample Size***

Leon, Davis, & Kraemer state that “power analyses should not be presented in an application for a pilot study that does not propose inferential results”. [40] Instead, we based our sample size on accepted practice for pilot studies, the considerable experience of the research team, and practical considerations.[40, 41]

## **Timeline**

The proposed study will last two years. During the initial 9 months we will develop the storytelling intervention; 12 months will be subsequently devoted to conducting the feasibility trial. The final three months will be devoted to data analysis, report and manuscript writing,

and planning the subsequent cluster-RCT.

### **Abbreviations**

CVD: Cardiovascular disease

HTN: hypertension

NCD: Non-communicable disease

WHO: World Health Organization

BP: Blood pressure

RCT: Randomized controlled trial

CHC: Community health center

DVD: Digital video disc

CSI: Culturally Sensitive Intervention

PI: Principal Investigator

JNC: Joint National Committee

CONSORT: Consolidated Standards of Reporting Trials

